### Reminder messages (baseline, 1 week and 2 weeks):

One week from baseline, and after 1 week and 2 weeks, participants will receive a reminder of their plans (in the volitional help sheet or detailed plan conditions) or a copy of the snacking tip sheet (in the passive control condition).

### Follow-up questionnaire (one month):

One month from baseline, participants will complete a follow-up questionnaire.

### The three conditions:

#### Volitional help sheet:

This consists of 4 steps that guide the user through the process of developing an appropriate plan.

- Step1: Sometimes we snack because we are hungry, but there are lots of other reasons too. Think about your snacks in the last week. Below is a list of ‘snack moments.’ These are times when people tend to choose unhealthy snacks or eat too much. Choose 3 snack moments from the list that happened to you the most often in the last week. [List of snack moments].
- Step 2: Below are your top 3 snack moments. Some snack moments will be more important than others. Choose the 1 that you would be happiest to change. [User chooses from 3 previously selected snack moments]
- Step 3: Great! Your most important snack moment was snacking because you are bored.
- The last step is to come up with a plan! Choose the solution that you think will work best for you. Drag it into the space on the right. [List of solutions]
- Step 4: Imagine how your plan might feel.[examples of scenarios when this might happen]. The final step is to make sure the plan is realistic. How hard do you think it will be to do this plan for the next month [Slider from very easy to very hard. If the user selects a number 7 they will be prompted to revise the plan]

#### Detailed plan:

Text: We want you to plan how you will change your unhealthy snacking behaviour each day because forming plans has been shown to improve snacking habits.

You are free to choose how you do this but we want you to formulate your plans in as much detail as possible. Please pay attention to the situations in which you will implement (carry out) these plans. Focus on situations when you are not hungry but find yourself snacking.

#### Snacking tips sheet:

This is a modified version of the NDSS Healthy snacking tips sheet with references to diabetes, blood glucose and carbohydrate removed (see https://static.diabetesaustralia.com.au/s/fileassets/diabetes-australia/201fcd3d-3b7c-4f5f-a81a-46a200b1fa84.pdf ).

### Primary Outcome:

The main outcomes to be measured will be maintenance self-efficacy (3 items, 4-point Likert scale anchored to not at all true/exactly true) and unhealthy snacking scores (based on self-reported diet during previous week).

### Secondary Outcomes:

Secondary outcomes to be measured will be action control and self-regulatory effort, a 5 item 7-point Likert scale (strongly disagree to strongly agree).

### Details of how data will be analysed:

Randomisation will be tested using MANOVA (multivariate analysis of variance), to ensure similarity across the three groups of participants in terms of demographic and other descriptive characteristics at baseline. The effect of the planning tools (volitional help sheet; detailed planning; information sheet) will be assessed using ANCOVA (analysis of covariance), controlling for: baseline values, age, sex, and language spoken at home. Orthogonal planned contrasts will be used to test if the volitional help sheet is superior to the detailed planning intervention, and if both of these interventions are superior to the passive control intervention (information sheet) on the primary outcomes. Secondary analyses will include exploring possible mediation of behavioural change by maintenance self-efficacy by using bootstrapping procedures as outlined in Preacher and Hayes (2008; BehavResMethods 40: 879-891). The potential moderating effect of health literacy on the efficacy of planning tools will be explored by examining the interaction of intervention and health literacy in ANCOVA.

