## Hypotheses:

1. Participants using the volitional help sheet will have higher maintenance self-efficacy scores than participants using the detailed planning intervention, and participants in these groups (averaged) will have higher scores than participants in the passive control group.

2. Participants using the volitional help sheet will have lower unhealthy snacking scores than participants using the detailed planning intervention, and participants in these groups (averaged) will have lower scores than participants in the passive control group.

3. Change in behaviour will be mediated by maintenance self-efficacy

4. The effects of planning tool will be moderated by health literacy. It is hypothesised that the volitional help sheet will be more useful (i.e. reduce unhealthy snacking to a greater extent) for people with lower healthy literacy than the detailed planning intervention

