## The intended sample size with a justification, and/or the participant sampling/selection strategy (as relevant to your study):

The intended sample size is approximately 435 participants. Piloting the survey will allow for a more definite sample size to be determined. Eighty-seven participants randomized to each group (totalling 261 participants) will yield ~90% power to detect moderate effect sizes (Cohen’s f = 0.25, corresponding to ANOVA effects and interaction as small as ?p 2 = 0.06) in the primary outcomes (maintenance self-efficacy scores; unhealthy snacking scores) and any secondary analyses, assuming a Bonferroni-adjusted two-sided alpha of 0.017 (allowing for four planned comparisons, and a correlation between the two primary outcome measures of ~ 0.25). Additionally, just under 50% additional cases will be recruited to account for potential missing values or attrition, totalling 435 participants (i.e., 145 per group).

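### The analysis section words the second contrast as showing both planning tools superior to control, but the contrast tests only their average

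*Protocol*

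**What the plan says.** The protocol describes the second contrast in two ways.

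- *Details of how data will be analysed*: the first of two orthogonal contrasts compares the help sheet with the detailed plan. The second is worded as asking "if both of these interventions are superior to the passive control intervention (information sheet) on the primary outcomes".
- *Hypotheses*, item 1 (maintenance self-efficacy): "participants in these groups (averaged) will have higher scores than participants in the passive control group". Item 2 (unhealthy snacking): "participants in these groups (averaged) will have lower scores than participants in the passive control group".

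The sample size section sets a Bonferroni-adjusted, two-sided level of 0.017 and gives its basis: "allowing for four planned comparisons, and a correlation between the two primary outcome measures of ~ 0.25". Two contrasts on each of two primary outcomes make four comparisons. That is a reading of the text, which does not list the four. The protocol describes no test of the help sheet alone, or of the detailed plan alone, against the snacking tips sheet.

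**The concern.** The two sections put different claims on the same test. Superiority of the average is a statement about one number, the mean of the two tool groups minus control. Superiority of both is a statement about two numbers, each of which must favour its tool. The first can be true while the second is false, because one effective tool can carry the average.

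The analysis section's description is the one likely to be carried into the report of results. If it is taken at face value, a significant second contrast would be reported as evidence for each tool, including one that may do nothing. The protocol intends the findings to inform the design of an app, so it matters which tool the evidence supports.

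**Working it through.** **1. What the second contrast is.** Order the arms as help sheet, detailed plan, control. The first contrast is (1, -1, 0). A second contrast (a, b, c) must satisfy a + b + c = 0 and, with equal groups, a - b = 0 for orthogonality. Hence a = b and c = -2a, which is (1/2, 1/2, -1) up to scale: the average of the tools minus control. This agrees with the Hypotheses section and not with the word used in the analysis section.

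**2. The plan's own figure.** Inputs from the sample size section: "Eighty-seven participants randomized to each group (totalling 261 participants) will yield ~90% power", to "detect moderate effect sizes (Cohen’s f = 0.25", at two-sided alpha 0.017. For the three-group F test, λ = f² × N = 0.0625 × 261 = 16.3, with 2 and 258 degrees of freedom. Power is 0.903, so the stated figure reproduces.

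**3. Standard errors, in SD units, at 87 per group.**
- Average versus control: √(1/174 + 1/87) = 0.131.
- Any two arms: √(2/87) = 0.152.
- Critical value for two-sided 0.017 on 258 degrees of freedom: t = 2.40.

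**4. Assumed effects.** The protocol gives no effect for each tool, so these are assumptions. Suppose one tool has effect d against control and the other has none. The arm means are d, 0 and 0, so f = d√2/3, and f = 0.25 gives d = 0.25 × 3/√2 = 0.53. The value 0.8 SD is a larger case (f = 0.8 × √2/3 = 0.38), and 0.5 SD is a slightly smaller one.

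**5. Chance of a significant result favouring the tools (noncentral t).** The noncentrality is (d/2)/0.131 for the average contrast and d/0.152 for tool versus tool. The last column comes from 400,000 simulated trials per case.

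| One tool | Other tool | Average vs control | Tool vs tool (effective one better) | Each tool beats control |
|---|---|---|---|---|
| 0.5 | 0 | 0.31 | 0.81 | about 0.008 |
| 0.53 | 0 | 0.35 | 0.86 | about 0.0085 |
| 0.8 | 0 | 0.74 | 0.998 | about 0.0086 |
| 0.5 | 0.5 | 0.92 | 0.009 | 0.71 |

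For example, at d = 0.53 the noncentrality of the average contrast is 0.265/0.131 = 2.02, and the power is 0.35.

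In the first three rows one tool is null, so a claim that both are superior is false. A significant average occurs in 31% to 74% of those trials. Requiring each tool to beat control succeeds in under 1%.

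**6. Gating on the average contrast.** If both tool-versus-control statistics exceed 2.40, the average contrast's statistic equals their mean multiplied by √(2/1.5) = 1.15, so it exceeds 2.40 as well. Testing the pairs only after a significant average therefore costs the claim for both no power. The simulation agrees: with both tools at 0.5 SD, 0.919 - 0.212 = 0.707, the same as the each-tool rule without a gate.

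**The case against.** The strongest reply is that this is loose wording and no more. The Hypotheses section says averaged twice, once for each primary outcome, and naming orthogonal contrasts fixes the same comparison. The hypothesis and the test therefore agree, and the word in the analysis section can be read as shorthand for the two tools taken together. Two orthogonal contrasts that match the hypotheses are a legitimate plan. This stands, and it limits the point to the conclusion attached to the test.

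A second reply is that the first contrast gives protection. With one null tool it would usually show that the tools differ (0.86 at 0.53 SD, 0.998 at 0.8 SD, when the help sheet is the effective one). This stands in part. Knowing that the tools differ does not tell the reader whether the weaker one beats control. At 0.8 SD against zero, both contrasts are significant together in about 74% of trials. Read literally, the analysis section would then report the help sheet as better and both tools as superior to control.

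Three stronger readings are tempting, and the document does not support them:
- *That the plan will declare an ineffective tool superior.* It has no decision rule that does so. The false conclusion arises only if the analysis section is read literally and the Hypotheses section is set aside.
- *That hypothesis 2 anticipates a tool with no effect.* It says only that the help sheet does better than the detailed plan. Help sheet better than detailed plan, and detailed plan better than control, satisfies it.
- *That the first aim goes unanswered.* The aim speaks of a planning tool in general terms, and the average against control addresses that.

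**Conclusion.** The point holds as a mismatch between the conclusion worded in the analysis section and the test that section specifies. The contrast supports a statement about the average of the two tools, and no planned test supports a statement about either one against control.

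The size depends on effects the protocol does not give. At 87 per group and two-sided alpha 0.017, with one tool null, the average contrast is significant about 35% of the time in the case that matches f = 0.25 and about 74% of the time at 0.8 SD. In those trials a reading of both superior would be wrong. These figures assume equal groups, a common SD and no gain in precision from the ANCOVA covariates.

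No error in the sample size follows: the stated power of about 90% reproduces. The correction is worth making because it is cheap and removes a conclusion that the analysis cannot support.

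**What to change.** 1. In *Details of how data will be analysed*, reword the second contrast so that it tests whether the average of the two planning interventions is superior to the passive control, matching the Hypotheses section.
2. Add two contrasts from the same ANCOVA, help sheet versus control and detailed plan versus control, tested only if the average contrast is significant.
3. Claim that both tools are superior only if both of these are significant at the contrast's level. Because both must succeed, this needs no further division of alpha.
4. Otherwise, limit the conclusion to the average.

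The cost is a change of wording and two extra contrasts, with no new data. The claim for both has lower power than the average: about 0.71 against 0.92 at 87 per group if both tools are at 0.5 SD. Reaching 90% power for it would take about 128 evaluable per group at 0.5 SD, or about 114 at 0.53 SD, so it should be presented as a claim the trial was not sized for. If the added contrasts are not wanted, step 1 and a sentence saying that no claim about an individual tool against control follows would be enough.

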### Potential significance of the study:

This proposed study will provide new data on online planning tools to assist with health behaviour change. The results will be examined in relation to participants’ health literacy levels to ascertain whether this may be a useful tool for this subgroup. Furthermore, findings from this study will inform the design of an app for assisting patients with diabetes to manage their health behaviours, including snacking behaviour.
